## Methods

### Trial Design

An open-label randomized controlled trial (RCT) will be carried out, in which patients are randomized to one of two groups at a 1:1 ratio: (1) conventional care with foot reflexology (40 patients) and (2) conventional care without foot reflexology (40 patients). Randomization is stratified on the type of cancer (digestive system or lung) and the presence or absence of metastases. The sponsor is the Hospices Civils de Lyon. The principal investigator is [name]. To design this trial, we used the CONSORT Statement for Randomized Trials of Nonpharmacologic Treatments [27].

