##### Self-Esteem

The benefits of foot reflexology on the level of self-esteem will be assessed at the end-of-study visit using the Body Image Questionnaire (BIQ) [33], which measures body image at a given time. The analysis of the BIQ takes into account the level of self-esteem assessed at the baseline using the Rosenberg scale [34].

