### Sample Size

In a study reported by Billhult et al [35], the mean improvement for CINV (measured using a VAS) was 49.5% in the placebo group, and 73.5% in the massage group (with a common standard deviation of 32.2%). Assuming these same hypotheses, for a two-sided risk of 5%, it is necessary to include 40 patients per group to demonstrate a statistically significant difference between the two groups with a power of 90%.

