### Type of Statistical Analysis Used

Study data are entered into a password-protected Excel spreadsheet (version 14.0, Microsoft Corp) accessible only to the project manager. Quantitative data will be described for the entire population, using the following descriptive statistics: the number, the number of missing values, the mean, the standard deviation, the median, the interquartile range, and the range. Qualitative variables will be summarized for the entire population using the following descriptive statistics: the frequency and percentage for each category of the variable and the missing values (missing values will be counted but are not included in the denominator of the calculation of frequencies).

For the primary endpoint, comparison of the relative change in the VAS between the two groups will be performed using a linear model adjusted on the type of cancer (digestive system or lung) and the presence of metastases (randomization stratification factors). This model allows the estimation of the difference in mean relative variation of VAS between the two groups, adjusted on potential confounding factors, with a 95% confidence interval. The VAS score may be transformed satisfy the assumptions of the linear model. If the assumptions of the model cannot be verified, the comparison between the two groups will be done using the van Elteren test. Specific estimates of the difference in relative VAS variation between the groups will be provided for both types of cancer, and by metastatic status.

The comparison of the frequency of episodes of CINV between chemotherapy cycles between the two groups will be performed using a mixed effects Poisson model, integrating the number of intercycle days as offset. The model will consider the intervention group and stratification criteria as fixed effects, and will incorporate one random intercept per patient.

The proportion of chemotherapy cycles in which the patient took at least one antiemetic drug will be compared between the two groups using a mixed effect logistic regression model. The model will consider the intervention arm and stratification criteria as fixed effects, and will incorporate one random intercept per patient.

The comparison of quality of life and anxiety between the two groups will be done using a Wilcoxon test.

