The comparison of self-image between the two groups will be done using a linear model adjusted on the baseline self-esteem evaluated with the Rosenberg scale. A possible transformation of the BIQ score will performed to satisfy the assumptions of the linear model.

The analysis will be performed according to the intention-to-treat principle, considering all patients that completed the endpoint evaluation in the group that was allocated to them by the randomization. The time point for the primary endpoint has been defined to minimize the risk of missing data.

For the primary endpoint, a secondary analysis will be performed per protocol, including patients with the endpoint assessment, and for whom the strategy allocated during randomization was fully implemented (ie, patients allocated to the foot reflexology group that did not receive four sessions of foot reflexology will be excluded from the analysis).

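### The body-image (BIQ) linear model names only baseline self-esteem as a covariate and omits both randomisation stratification factors; if those factors predict BIQ, its interval and test will be conservative

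*Protocol article*

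**What the plan says.** Under Trial Design the protocol article states: "Randomization is stratified on the type of cancer (digestive system or lung) and the presence or absence of metastases". Allocation is 1:1 with 40 patients planned per group.

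The section Type of Statistical Analysis Used carries both factors into three models:

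- The primary VAS comparison is a "linear model adjusted on the type of cancer (digestive system or lung) and the presence of metastases (randomization stratification factors".
- For the Poisson model of episode frequency: "The model will consider the intervention group and stratification criteria as fixed effects, and will incorporate one random intercept per patient".
- For the logistic model of antiemetic use: "The model will consider the intervention arm and stratification criteria as fixed effects, and will incorporate one random intercept per patient".

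For the BIQ, the same section says: "The comparison of self-image between the two groups will be done using a linear model adjusted on the baseline self-esteem evaluated with the Rosenberg scale". The Self-Esteem section agrees: "The analysis of the BIQ takes into account the level of self-esteem assessed at the baseline using the Rosenberg scale". Neither place mentions cancer type or metastases for this model, and no reason is given for leaving them out.

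**The concern.** When allocation is stratified, the strata are balanced between the arms by design. Differences in outcome between strata then contribute almost nothing to the true sampling error of the group difference. A linear model without the strata still counts that variation as residual noise. If the strata are prognostic, its standard error overstates the real uncertainty, the 95% interval covers more than 95%, and the test rejects less often than its nominal 5%.

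The BIQ is the only end-of-study measure named for the self-esteem objective, and the sample size was set for the VAS, so no power was reserved for the BIQ. A covariate-adjusted linear model is already planned here, and it can take the two factors directly. This is also not a detail simply left to a fuller document: the article states a covariate for this model in the section where it lists the strata for three others, and an analyst following the text would fit group plus Rosenberg.

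**Working it through.** **The plan's own figure.** The Sample Size section gives 40 per group for the VAS, from a difference of 73.5 − 49.5 = 24.0 points, SD 32.2, two-sided 5% and 90% power. The normal formula gives n = 2 × (1.96 + 1.2816)² × 32.2² / 24.0² ≈ 37.8, so 38 per group; the t-based calculation gives 39. Power at 40 is 91.5% (normal) or 90.9% (t). The figure is sound, but it concerns the VAS and does not bear on the BIQ.

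**Inputs for the BIQ.** From the article: two binary strata, 1:1 allocation, 80 patients, two-sided 5%. Not in the article, so assumed: R2, the share of BIQ variance left after Rosenberg that the two factors explain.

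**Closed form.** With strata perfectly balanced, Var(true) = (1 − R2) × Var(model without strata). Hence

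- type I error = 2 × [1 − Φ(1.96 / √(1 − R2))], which is 3.9%, 2.8% and 1.9% at R2 = 0.1, 0.2 and 0.3;
- interval width ratio = 1 / √(1 − R2), which is 1.054, 1.118 and 1.195.

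**Simulation.** There were 8,000 trials of 80 patients per setting. Further assumptions: permuted blocks of 4 within the four strata, half lung cancer, 60% metastatic, Rosenberg–BIQ correlation 0.4, R2 shared equally by the two factors, and a true effect of 0 or 0.6 SD (the SD left after Rosenberg).

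| R2 | Type I error, strata omitted / included | Interval width, omitted ÷ included | Power at 0.6 SD, omitted / included |
|---|---|---|---|
| 0 | 4.8% / 4.9% | 1.00 | 74.8% / 75.0% |
| 0.05 | 3.9% / 4.6% | 1.03 | 75.3% / 76.9% |
| 0.10 | 4.2% / 5.3% | 1.05 | 75.8% / 78.8% |
| 0.20 | 3.0% / 5.0% | 1.12 | 77.4% / 83.9% |
| 0.30 | 1.9% / 4.8% | 1.20 | 77.7% / 87.9% |

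The simulation error on a 5% rate is √(0.05 × 0.95 / 8,000) ≈ 0.24 points, so the order of the type I errors at R2 = 0.05 and 0.10 is noise.

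**Where the loss sits.** At R2 = 0.2 with no true effect, the model without strata reports a mean standard error of 0.225, while its estimates actually vary with a standard error of 0.203. With strata included, the actual figure is 0.201. The estimator is almost equally precise either way; what is inflated is the reported uncertainty.

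**The case against.** **The effect is conditional.** A reader might infer that the BIQ interval and p-value are too conservative as planned, and that precision is lost. The article does not support that. Nothing in it says that cancer type or metastatic status predicts body image once self-esteem is accounted for, and at R2 = 0 the two models behave alike. Even with prognostic strata, the true sampling error barely moves (0.203 against 0.201). Nor should a reader infer bias from the article's description of the strata as potential confounders: allocation is randomised and the group estimate is unbiased without them. This objection stands in full.

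**Large R2 values are demanding.** For one factor split 50/50 that shifts BIQ by δ within-stratum SDs, R2 = (δ²/4) / (1 + δ²/4). R2 = 0.2 then needs δ = 1.0, or about 0.71 from each of two such factors. The treatment effect planned for the VAS is 24.0 / 32.2 = 0.745 SD. R2 = 0.05 already needs δ = 0.46. The lower rows of the table therefore deserve the most weight.

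**The power gain depends on the effect chosen.** No BIQ effect is stated. At 0.745 SD, borrowed from the VAS, the normal approximation gives gains of only 1.4, 2.4 and 2.9 points at R2 = 0.1, 0.2 and 0.3. The block size is not given either.

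**The inconsistency follows a pattern.** The three models with strata all concern nausea, vomiting or antiemetic use. None of the three questionnaire outcomes is strata-adjusted; quality of life and anxiety are compared by Wilcoxon tests. The article also does not say that Rosenberg is the sole covariate, and the full plan may add others. This softens the charge of a stray omission, but the article gives no reason for the pattern, and the BIQ is the questionnaire outcome for which a linear model is already planned.

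**Conclusion.** The point holds as a minor one on a secondary outcome. The covariate stated for the BIQ model leaves out both stratification factors, unlike the three models for nausea, vomiting and antiemetic use. If the factors predict BIQ beyond Rosenberg, the reported standard error, interval and p-value will be conservative and some power is given up. Any error runs against a false claim of benefit.

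The size rests on an R2 that the article does not give:

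- R2 = 0: no material effect.
- R2 = 0.05 to 0.1: intervals about 3% to 5% wider, and about 2 to 3 points of power lost at an assumed 0.6 SD effect.
- R2 = 0.2: intervals about 12% wider and type I error near 3%; this needs strata effects on body image that nothing in the article establishes.

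The simulated figures also assume blocks of 4 and complete BIQ data on 80 patients.

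**What to change.** In Type of Statistical Analysis Used, state that the BIQ linear model is adjusted for baseline Rosenberg self-esteem, type of cancer and presence of metastases, and that the adjusted mean difference is reported with its 95% confidence interval. Settle this before the data are analysed, so that the covariates are not chosen with results in view.

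The cost is one sentence and two residual degrees of freedom: 80 − 3 = 77 falls to 80 − 5 = 75 if all 80 patients provide a BIQ. No new data are needed, because both factors are recorded for randomisation. If the factors turn out not to be prognostic, nothing material is lost (simulated power 75.0% with them, 74.8% without).

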### Description of Processes, Interventions, and Comparisons

The patients randomized to the intervention group will benefit from a foot reflexology session (30 minutes) at each chemotherapy session for four cycles. The reflexology sessions will be given during chemotherapy infusion every 2 or 3 weeks, depending on the chemotherapy protocol. The sessions will be administered by two qualified reflexologists (they were trained at the French school École des Techniques en Réflexologie).

In a meta-analysis study, Lee et al [28] determined that the optimal comparator is a control group with conventional care without foot reflexology or massage therapy.

Foot reflexology is CAM, based on the principle of acupressure, that helps the body restore homeostasis. It is a holistic approach that allows one to understand the body as a whole. Each part of the body is represented by a zone or reflex point on the foot. The reflexologist stimulates each reflex zone using specific thumb and finger techniques on the patient’s feet. Depending on the objective, the zones on the feet are stimulated using different types of pressure. During a session focused on the treatment of CINV, the reflexologist mainly stimulates the reflex points related to the digestive system, the lymphatic system, and kidneys to help the body eliminate toxins. The reflexology chart used in this clinical study is based on the one proposed by Eunice Ingham [29].

The reflex zones of the whole body are also found on the hands. During the first reflexology session, the reflexologist shows the patient the appropriate zones on the hands to relieve nausea. The patient will be able to stimulate these reflex points between each cycle if necessary (self-practice at home). Adherence of participants to reflexology is assessed with a diary. They have been instructed to use a diary every day between each cycle of chemotherapy to note episodes of nausea and vomiting. They also note if they took at least one antiemetic drug (on-demand treatment). If the patient uses self-massage, they note whether it has been effective.

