### Evaluation Criteria

#### Primary Outcome

The primary outcome is the relative change in the severity of nausea and vomiting, as assessed with a visual analogue scale (VAS). The patient is asked to mark their current nausea level on the horizontal line with anchor statements on the left (a happy face, no nausea=0 mm) and on the right (a very sick green face, paroxysm of nausea or vomiting=100 mm). Unlike vomiting, which is measurable by the number of episodes per day, nausea is a subjective experience. For that reason, we will use a VAS to evaluate the severity of nausea in patients [30]. For patients in the intervention group, this measurement will be done when the patient arrives at the outpatient or inpatient department and after the foot reflexology session, during the second cycle of chemotherapy. For patients in the control group, this measurement will be done when the patient arrives at the outpatient or inpatient department and before leaving the hospital, during the second cycle of chemotherapy. The assessment is performed by a nurse or clinical research assistant.

All patients will continue to receive standard antiemetic drugs (eg, 5-hydroxytryptamine 3 receptor antagonists, dexamethasone, and neurokinin-1 inhibitor receptor antagonists). According to chemotherapy protocols, oral antiemetic agents are included, and patients are instructed to complete the course.

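### The secondary per-protocol analysis of the cycle-2 VAS endpoint selects the reflexology arm on sessions given after the endpoint, with no matching condition stated for controls

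*Protocol article*

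**What the plan says.** Three parts of the protocol article's Methods bear on this.

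- **Timing of the endpoint** (Primary Outcome). The VAS is read twice at one visit. In the reflexology arm the second reading comes "after the foot reflexology session, during the second cycle of chemotherapy". In the control arm it comes "before leaving the hospital, during the second cycle of chemotherapy".
- **Schedule of the intervention** (Description of Processes, Interventions, and Comparisons). Patients receive a "foot reflexology session (30 minutes) at each chemotherapy session for four cycles", with sessions two or three weeks apart.
- **Per-protocol set** (Type of Statistical Analysis Used). The analysis is explicitly tied to this endpoint: "For the primary endpoint, a secondary analysis will be performed per protocol". The general rule is "including patients with the endpoint assessment, and for whom the strategy allocated during randomization was fully implemented". A clause introduced by ie then spells it out: "patients allocated to the foot reflexology group that did not receive four sessions of foot reflexology will be excluded from the analysis". Nothing comparable is given for the control arm.

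The same section says that the time point was chosen to keep missing data low. It also defines the intention-to-treat set as all patients with the endpoint evaluated, in their randomised group.

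**The concern.** Whether a patient goes on to sessions 3 and 4 is settled weeks after the primary endpoint is complete. Using it to decide who enters an analysis of that endpoint conditions on the future, and the stated rule does so in one arm only.

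The selection need not be neutral. Sessions are given during the infusion, so a patient who stops chemotherapy also loses the remaining sessions. The Background section says that chemotherapy-induced nausea and vomiting can lead to treatment being postponed or stopped. In an open-label trial, patients who feel no benefit may also decline further sessions. Either route would remove poorer responders from the reflexology arm while comparable controls stay in.

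At stake is the use of the per-protocol result as corroboration. A reader who sees it agree with the intention-to-treat result, or exceed it, will take that as support, and part of the agreement could come from the exclusion rule.

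**Working it through.** **1. The plan's own figure.** The Sample Size section gives mean improvements of 49.5% and 73.5%, a common SD of 32.2%, a two-sided 5% level and 90% power. The difference is 73.5 − 49.5 = 24 points.

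n per group = 2 × (1.960 + 1.282)² × (32.2/24)² ≈ 37.8, so 38 (39 with the t distribution).

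The stated 40 per group is consistent with this. Power at 40 per group is 91.5% (normal) or 90.9% (t). The SD of 32.2 and the difference of 24 are used below as the scale.

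**2. Two patients compared.** Both have complete cycle-2 readings, and both stop chemotherapy before cycle 4.

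| | Reflexology patient | Control patient |
|---|---|---|
| Allocated care delivered up to the endpoint | yes (sessions 1 and 2) | yes (no reflexology) |
| Endpoint assessed | yes | yes |
| Four sessions received | no | not applicable |
| Per-protocol set under the stated clause | excluded | no exclusion stated |

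**3. Size if stopping relates to response.** Let q be the fraction of the reflexology arm excluded, and rho the correlation between the tendency to continue and the cycle-2 improvement. The document gives neither; both are assumptions. With a normal outcome, no true effect and exclusion of the lowest fraction q on the latent tendency to continue:

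bias = 32.2 × rho × φ(z_q) / (1 − q)

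- q = 10%, rho = 0.2: 32.2 × 0.2 × 0.1755/0.9 = +1.3
- q = 20%, rho = 0.4: 32.2 × 0.4 × 0.2800/0.8 = +4.5
- q = 30%, rho = 0.6: 32.2 × 0.6 × 0.3477/0.7 = +9.6

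The type I errors come from simulating 20,000 trials per scenario, with 40 per arm before exclusion and a two-sided t-test. The simulation omits the stratification adjustment of the planned linear model.

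| q | rho | Bias, points | Type I error of this analysis |
|---|---|---|---|
| 10% | 0 | 0 | 5.1% |
| 10% | 0.2 | +1.3 | 5.3% |
| 10% | 0.4 | +2.5 | 6.2% |
| 10% | 0.6 | +3.8 | 7.8% |
| 20% | 0 | 0 | 5.1% |
| 20% | 0.2 | +2.3 | 5.8% |
| 20% | 0.4 | +4.5 | 8.9% |
| 20% | 0.6 | +6.8 | 14.8% |
| 30% | 0 | 0 | 4.8% |
| 30% | 0.2 | +3.2 | 6.9% |
| 30% | 0.4 | +6.4 | 12.4% |
| 30% | 0.6 | +9.6 | 23.4% |

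The formula is linear in rho, so a negative rho reverses the sign: q = 20% with rho = −0.4 gives −4.5 points.

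**4. Contrast with a symmetric rule.** When the same completion rule and the same drop-out mechanism apply to both arms, the simulated bias lies between −0.14 and +0.09 points and the type I error between 4.7% and 5.2%. Under this model the bias comes from excluding in one arm only.

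**5. Cost even without bias.** Excluding 10%, 20% or 30% of one arm leaves 36, 32 or 28 reflexology patients. Normal-approximation power at the design difference then falls from 91.5% to 90.0%, 88.2% or 85.7%, although the excluded patients had valid readings.

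**The case against.** Several counter-arguments have weight.

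- **The analysis is secondary.** This stands. A reader might infer that the trial's main conclusion or its error rate is compromised. The documents do not support that: the primary comparison keeps every patient with the endpoint in the randomised arm, whatever happened at cycles 3 and 4. The type I errors above belong to the per-protocol analysis alone.
- **The direction is not established.** This also stands. It is tempting to say that the analysis is biased towards reflexology. The endpoint, however, is a relative change within one hospital visit, and the protocol reports neither the reasons for stopping nor any link between that change and later stopping. Sessions missed for scheduling reasons could be unrelated to response. The Background statement on discontinuation makes a bias in favour of reflexology plausible but does not demonstrate it.
- **Controls are not necessarily all kept.** This stands in part. The general requirement of full implementation is worded for both arms, and a control who received reflexology might be removed under it. The clause that explains the requirement nevertheless names only the reflexology arm and gives controls no counterpart to the four-session rule.
- **Four sessions is the protocol's own definition of full delivery, and control adherence may be detailed in the full protocol or SAP.** The first part is true, but a definition suited to the whole course does not suit an endpoint reached halfway through it. As to the second, the point concerns a rule that the article states, not one that it leaves out.

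**Conclusion.** The point holds as a moderate issue. The per-protocol rule does not fit the endpoint it is applied to: it selects the reflexology arm on events after the cycle-2 reading, with no matching condition stated for controls. That much follows from the text without any assumption.

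Whether bias results, and how much, depends on why later sessions are missed. Over the assumed ranges (10% to 30% excluded, correlation 0.2 to 0.6) it is about +1 to +10 points against a design difference of 24. At the mild end the inflation of type I error is negligible; at the severe end it is large. As written, the analysis cannot be relied on to corroborate the primary result.

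**What to change.** For the VAS endpoint, define the per-protocol set by what happened up to the cycle-2 reading:

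- reflexology arm: the sessions at cycles 1 and 2 were received;
- control arm: no reflexology was received up to cycle 2;
- both arms: cycle 2 was given and both VAS readings are present.

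If a four-session rule is wanted, keep it for end-of-study outcomes and pair it with four chemotherapy cycles received in controls.

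The change is a sentence or two in the protocol and in the SAP, made before the analysis. It needs no new data, and it keeps reflexology patients who have valid cycle-2 readings and would otherwise be dropped. The primary analysis and the sample size stay as they are.
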